## Abstract

**OBJECTIVES::**

We designed a cohort study to describe characteristics and outcomes of patients with coronavirus disease (COVID-19) admitted to the intensive care unit (ICU) in the largest public hospital in Sao Paulo, Brazil, as Latin America becomes the epicenter of the pandemic.

**METHODS::**

This is the protocol for a study being conducted at an academic hospital in Brazil with 300 adult ICU beds dedicated to COVID-19 patients. We will include adult patients admitted to the ICU with suspected or confirmed COVID-19 during the study period. The main outcome is ICU survival at 28 days. Data will be collected prospectively and retrospectively by trained investigators from the hospital’s electronic medical records, using an electronic data capture tool. We will collect data on demographics, comorbidities, severity of disease, and laboratorial test results at admission. Information on the need for advanced life support and ventilator parameters will be collected during ICU stay. Patients will be followed up for 28 days in the ICU and 60 days in the hospital. We will plot Kaplan-Meier curves to estimate ICU and hospital survival and perform survival analysis using the Cox proportional hazards model to identify the main risk factors for mortality. ClinicalTrials.gov: NCT04378582.

**RESULTS::**

We expect to include a large sample of patients with COVID-19 admitted to the ICU and to be able to provide data on admission characteristics, use of advanced life support, ICU survival at 28 days, and hospital survival at 60 days.

**CONCLUSIONS::**

This study will provide epidemiological data about critically ill patients with COVID-19 in Brazil, which could inform health policy and resource allocation in low- and middle-income countries.

## INTRODUCTION

In December 2019, an outbreak of severe acute respiratory syndrome (SARS) attributed to a new coronavirus, namely, severe acute respiratory syndrome coronavirus-2 (SARS-CoV-2), was identified in the Wuhan region of China (1-3). The disease caused by the virus, called coronavirus disease (COVID-19), is characterized by a flu-like syndrome, with symptoms such as fever, cough, myalgia, and gastrointestinal symptoms (4). Most cases are mild, some may be asymptomatic, but approximately 15% of patients have a more severe presentation, and approximately 5% are critical (5). The acute respiratory failure among critically ill patients with COVID-19 is unique in its presentation: difficult-to-treat hypoxemia, clotting disorders, renal failure, and changes in immunity and inflammatory phenomena (6-8) all pose challenges to the management of these patients.

The virus spread from China to Europe and then the Americas, causing more than 20 million cases and hundreds of thousands of deaths as of August 15^th^ (9). Brazil is one of the countries with the highest number of cases as well as deaths, and Sao Paulo is currently the state with highest number of cases in the country (10), with over 26,000 deaths by mid-August.

Reports of the most important risks factors and mortality rates have become available (11-17), but as Latin America emerges as the new hotspot of the pandemic, there are no epidemiological data on COVID-19 or any epidemic of this magnitude in low- and middle-income countries (LMICs) that could help predict the impact of the new disease on its health system. The burden of critical illness is higher in LMICs (18), and the mortality of patients on mechanical ventilation in Brazil is high (19). Given the differences in the age distribution of the population, intensive care unit (ICU) capacity, lower availability of diagnostic testing for the new virus, difficulties in the implementation of public measures to mitigate virus spread in highly populated cities, and delayed access to health care, the burden of COVID-19 tends to be higher in LMICs than in high-income countries (HIC).

Knowing the characteristics of critically ill patients with COVID-19 and their clinical outcomes in LMICs is extremely important to inform clinical decision-making and public health management in this setting. Therefore, we designed an observational study to describe the characteristics and outcomes of patients admitted to the ICUs of the largest public hospital in Sao Paulo during the peak of the COVID-19 pandemic in Brazil.

## MATERIALS AND METHODS

### Study design and location

This is a cohort study conducted at Hospital das Clínicas from University of Sao Paulo Medical School. It is the largest academic, tertiary, university-affiliated hospital in Brazil with 300 adult ICU beds dedicated exclusively to the care of COVID-19 patients during the peak of the pandemic in Sao Paulo.

The Research Ethics Committee of Hospital das Clínicas da Universidade de Sao Paulo approved the study protocol (number 31382620.0.0000.0068), and the study was registered in a public database (clinicaltrials.gov, NCT04378582). The requirement for informed consent was waived because of the observational nature of the study.

From March 13 to April 16, 200 previously functioning ICU beds were converted into COVID-19-dedicated ICU beds. In the following 45 days, operating rooms and several hospital wards were repurposed to accommodate 100 additional COVID-19-ICU beds. Physicians, nurses, and respiratory therapists were hired to constitute new ICU teams dedicated to patients occupying these additional beds. New staff were trained and distributed within experienced ICU teams.

The study is observational, and patient care was carried out following institutional protocols developed specifically for COVID-19 patients. The protocol recommends routine use of deep venous thrombosis prophylaxis and systemic antibiotics if bacterial coinfection is suspected. Specific drugs for treating SARS-CoV-2 were not recommended but could be administered at the discretion of the attending physician. The study also included specific protocols for the ventilatory management of respiratory failure and for sedation management throughout ICU stay. Other critical care standards were not changed during the pandemic.

### Study population

We will include all consecutive adult patients with suspected or confirmed COVID-19 admitted to the ICUs between March 30 and June 30, 2020 with an expected ICU stay longer than 24 hours (Figure 1). The only exclusion criterion is ICU stay shorter than 24 hours. Patients readmitted to the ICU during their hospital stay will be included in the study only at their first ICU admission. Patients will be classified as confirmed COVID-19, highly suspected COVID-19 without laboratory confirmation, and ruled-out COVID-19. Positive results on either an RT-PCR assay of nasal specimens, throat-swab specimens, or tracheal aspirate or a serologic (antibody) test will be used to confirm SARS-CoV-2 infection. Patients highly suspected of having an infection but with negative RT-PCR test results initially will be submitted to a second RT-PCR test and/or a serologic test after seven days of symptom onset. Patients with ruled-out SARS-CoV-2 infection will be transferred to another facility in the same institution and will be excluded from analysis.

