### Outcomes

The main outcome is ICU survival at 28 days. Secondary outcomes include duration of mechanical ventilation, need for rescue therapies for severe hypoxemia, need for renal replacement therapy, ICU complications, and hospital survival at 60 days.

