Categorical variables will be expressed as counts and percentages, and continuous variables, as mean (standard deviation) or median (interquartile range), as appropriate. All hypothesis tests will be two-tailed, with a significance level of 0.05, and they will be performed using the R software (R Core Team, 2016, Vienna, Austria). We will build Kaplan-Meier curves to estimate 28-days survival. ICU survival will be defined as the time interval between ICU admission and patient death from any cause or ICU discharge. Time will be censored at 28 days for patients who are still alive. Hospital survival will be defined as the time interval between ICU admission and patient death from any cause or hospital discharge. Patients discharged home will be considered alive at day 28. We will perform survival analysis using the Cox proportional hazards model censored at 28 days to identify the main risk factors for ICU survival beyond expected associations, such as age, comorbidity burden, and severity of disease at ICU admission. Variables identified *a priori* as clinically relevant (Table 5) and additional variables with a *p*-value <0.20 in a univariate analysis will be evaluated as independent risk factors of poor prognosis in a multivariable Cox model. The order of inclusion of variables into Cox multivariable models will follow statistical significance criteria and clinical relevance. Alternative models will be chosen on the basis of information criteria and likelihood ratio-based tests. Wherever possible, continuous variables will be modeled to account for nonlinearity with splines or polynomials and avoiding dichotomization. Additivity will be addressed with interaction terms. The proportional hazards assumption will be tested using Schoenfeld residuals. We will use mixed models to analyze the impact of ventilatory variables collected during hospitalization on the main clinical outcomes. We will perform complete case analyses, without missing data. We will also perform a sensitivity analysis using multiple imputation.

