## DISCUSSION

Our study will report characteristics and outcomes of all patients admitted to the ICU at the largest academic hospital in Brazil during the peak of the pandemic of COVID-19 in Sao Paulo. The hospital developed a preparedness plan that included grouping COVID-19 patients in a building dedicated exclusively for the care of these patients, creation of surge ICUs to increase ICU bed capacity, and hiring additional healthcare professionals to work exclusively in the COVID-19 ICUs. The actions were coordinated by a crisis committee composed of critical care specialists, pulmonologists, infectious disease specialists, nurses, respiratory specialists, pharmacists, engineers, and administrators, among others, who met daily to make shared decisions. Such an effort helped prevent shortage of personal protective equipment and important medications, facilitated the development of institutional protocols for patient care and infection control, and contributed to a rational distribution of limited resources with potential impact on patient outcomes (28). The results will allow for the assessment of clinical outcomes of critically ill patients that will be representative of a middle-income country in a highly strained environment caused by the pandemic. Overall healthcare inequity in the treatment of chronic comorbidities in the Brazilian healthcare system, delayed access to proper critical care, and heterogeneity in ICU within the hospital (surge *vs.* previously functioning ICUs) are some of the system-level characteristics that highlight the importance of this study to assess overall survival of COVID-19 patients in LMICs.

We will also be able to assess resource utilization beyond mechanical ventilation, such as renal replacement therapy and ICU length of stay, to characterize the burden of this surge of severe respiratory failure patients to our hospital and healthcare system. In the main manuscript, both characterization of the cohort and the risk factors for increased mortality will be assessed and compared to the current literature. Our main benchmark for ICU and hospital survival is the result published regularly by the Intensive Care National Audit & Research Centre (ICNARC), that is, 35%-45% hospital mortality among patients receiving mechanical ventilation (29), which represents the outcomes of a universal healthcare system in a HIC.

In addition, the study will provide answers to many ancillary research questions:

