Arterial lactate (mg/dL)	mean (SD)	mean (SD)	
pH	mean (SD)	mean (SD)	

**p*-value will come from univariate Cox proportional hazards model.

^#^During the first 24h of ICU stay.

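### Excluding actual ICU stays under 24 hours removes first-day deaths from a survival clock that starts at ICU admission, so the main estimate is conditional on a 24-hour stay but not labelled so

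*Protocol article*

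**What the plan says.** Under Study population, the sampling frame is stated as "We will include all consecutive adult patients with suspected or confirmed COVID-19 admitted to the ICUs" in the study window, "with an expected ICU stay longer than 24 hours". The next sentence reads "The only exclusion criterion is ICU stay shorter than 24 hours". It does not use the word expected and makes no exception for patients who die.

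Under Outcomes, "The main outcome is ICU survival at 28 days". The Statistical analysis plan section sets the clock: "ICU survival will be defined as the time interval between ICU admission and patient death from any cause or ICU discharge", and "Time will be censored at 28 days for patients who are still alive". Hospital survival also runs from ICU admission. No 24-hour landmark or delayed entry is stated.

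The Table 5 footnote gives the window for the acuity covariates: "During the first 24h of ICU stay". The Discussion describes the scope: "Our study will report characteristics and outcomes of all patients admitted to the ICU".

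**The concern.** The inclusion rule uses a forecast made at admission. The exclusion rule, as written, uses what happened afterwards. For patients whose stay goes as expected, the two rules agree. They part for patients who were expected to stay longer but died or left within 24 hours, and for those who died the exclusion selects on the outcome itself.

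With time zero at ICU admission, every analysed patient is guaranteed to survive the first day. The Kaplan-Meier curve is flat over that day by construction, and the day-28 estimate answers a narrower question than its label says. The article also plans to set its mortality against an external benchmark and to compare surge with previously functioning ICUs. Both comparisons depend on which deaths are counted.

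**Working it through.** **Logical check.** Take a patient expected to stay several days who dies at hour 10.

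- Inclusion (expected stay over 24 h): met.
- Exclusion (stay under 24 h): applies, so the patient is removed.
- Survival clock: would have started at ICU admission, with death as an event at hour 10. That event is lost.

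Every such death is lost in the same way, from ICU survival and from hospital survival.

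**Size.** The plan gives no figure that can be reproduced here: 300 and 500 are anticipated sample sizes, and early deaths and early discharges are not counted. What follows is an illustration on assumed inputs, treating mortality as a simple proportion and early live discharges as 28-day survivors.

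- m = true 28-day mortality. Assumed 40%, the middle of the 35% to 45% hospital mortality in ventilated patients that the Discussion uses as its benchmark.
- e = share of admissions dying within 24 h. Assumed 2%, 5% or 8%.
- d = share leaving the ICU alive within 24 h. Assumed 0% or 3%.

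Reported mortality = (m − e) / (1 − e − d).

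| e | d = 0 | Shift (points) | d = 3% | Shift (points) |
|---|---|---|---|---|
| 2% | 0.38/0.98 = 38.8% | −1.2 | 0.38/0.95 = 40.0% | 0.0 |
| 5% | 0.35/0.95 = 36.8% | −3.2 | 0.35/0.92 = 38.0% | −2.0 |
| 8% | 0.32/0.92 = 34.8% | −5.2 | 0.32/0.89 = 36.0% | −4.0 |

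With fewer early deaths the sign reverses: e = 1% and d = 3% gives 0.39/0.96 = 40.6%, a shift of +0.6 points.

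**Break-even.** The shift is zero when e(1 − m) = d·m. At m = 40% that is e = 0.67d, or 1.5 early live discharges for each early death. With fewer discharges than that, reported mortality is too low. With more, it is too high.

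**Sensitivity to m.** With 500 admissions, m = 35% or 45% and e between 1% and 5%, losing early deaths alone shifts mortality by −0.6 to −3.4 points and removes about 2% to 14% of all deaths. If 3% to 5% of admissions also leave alive within 24 h, the net shift runs from −2.4 to +1.8 points.

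**Against sampling error.** At 40% and n = 500, SE = √(0.4 × 0.6 / 500) = 2.2 points. The early-deaths-only shifts of 1.2, 3.2 and 5.2 points are about 0.6, 1.4 and 2.4 SE. Unlike the SE, they do not shrink in a larger cohort.

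**Cox model.** If everyone analysed is in the ICU at 24 h, no event falls on day 1. Moving a common origin from admission to 24 h, with the same end of follow-up, leaves the order of events and the risk sets unchanged. The hazard ratios are the same, and only their label needs to say that they are conditional.

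**The case against.** A reader might infer more than the text supports, and four objections limit the point.

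- **The rules contradict each other.** They need not. An exclusion on actual stay can simply narrow an inclusion on expected stay. The exclusion may also be loose wording for expected stay, in which case early deaths are kept and one word is missing. This stands as a limit. Even so, data collectors will apply the sentence as written, and it needs settling either way.
- **Survival will certainly look too good.** The documents do not show this. Early live discharges are removed too, and their number is not given. Screening on expected stay should make them uncommon, but that is an inference.
- **The Cox model suffers immortal-time bias.** It does not. The guaranteed day is common to all patients, and a 24-hour minimum suits covariates measured over that day.
- **The lost patients are the sickest or latest to arrive.** Nothing in the documents establishes this. The Discussion names delayed access to critical care as part of the setting, not as something to be measured.

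It is also fair to say that the restriction is stated openly, that a 24-hour minimum is legitimate for a declared conditional estimate, and that the participant flow in Figure 1 is not shown and may already list these exclusions. None of this changes the fact that the main outcome is timed from admission and is not declared conditional.

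**Conclusion.** The point holds for the descriptive survival results. Followed as written, the exclusion drops every death in the first 24 hours, so the 28-day ICU and 60-day hospital survival estimates are conditional on a 24-hour ICU stay while being described as covering all admitted patients.

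The size cannot be fixed from the documents. On the assumption of 40% true mortality and 2% to 8% early deaths, losing early deaths alone lowers reported mortality by 1.2 to 5.2 points. Once early live discharges are removed as well, the net direction is uncertain. The conclusion rests on reading the exclusion literally, as actual stay.

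**What to change.** 1. Rest eligibility on information available at admission. Drop the exclusion on actual stay for the Kaplan-Meier and mortality estimates, and count deaths before 24 h as events.
2. Restore early live discharges together with early deaths. Restoring only the deaths would push the estimate the other way: at m = 40% and d = 3%, 0.40/0.97 = 41.2%.
3. Keep the 24-hour minimum only as an explicit landmark for the Cox model (alive and in the ICU at 24 h), and label its results as conditional.
4. Report all stays under 24 h by vital status, for example in the participant flow.
5. For March 30 to May 5, when data are collected retrospectively, expected stay may be hard to recover and could be judged with the outcome known. List all admissions under 24 h by vital status, and add a sensitivity analysis that includes all of them.
6. Align the scope sentence in the Discussion with the population finally chosen.

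The cost is a short abstraction from existing records under the existing consent waiver. Day-1 laboratory and ventilator data will be sparse for these patients, which matters little if they enter only the survival estimates and not the landmark model.

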### Outcomes

The main outcome is ICU survival at 28 days. Secondary outcomes include duration of mechanical ventilation, need for rescue therapies for severe hypoxemia, need for renal replacement therapy, ICU complications, and hospital survival at 60 days.

### Data collection, management, and quality control

Data will be collected prospectively from study approval (May 6) to August 30, 2020 and retrospectively from March 30 to May 5, 2020. Trained data collectors will retrieve patient information from the hospital electronic medical records, and at the bedside (Figure 2). Study data will be collected and managed using a secure, web-based data collection platform (REDCap - Research Electronic Data Capture) (20,21). Data collected include demographic information, race, initial symptoms, comorbidities, outpatient medications, simplified acute physiology score (SAPS 3) (22,23), and laboratorial test results at admission (Table 1 and 2). We will also collect data on the Sequential Organ Failure Assessment score (SOFA) (24), need for oxygen support, mechanical ventilator parameters, use of specific interventions to treat SARS-CoV-2 infection, and decision to withhold or withdraw life support (Table 3). Patients will be followed up for 28 days, and data on exposures and outcomes, such as use of non-invasive ventilation, use of a high-flow nasal cannula, number of days on mechanical ventilation, need for renal replacement therapy, tracheostomy, occurrence of thromboembolic events, use of prone positioning or extracorporeal membrane oxygenation (ECMO) support, and ICU discharge status, will be collected (Table 4). We will follow up patients to register vital status at 60 days or at hospital discharge, whichever occurs first.

Quality control measures will include the use of REDCap-based structured data collection forms, training data collectors to ensure data completeness and consistency, and data management processes within the platform to deal with missing data, outliers, and data collection mistakes.

We will report study results in accordance to recommended guidelines for reporting observational studies, the Strengthening The Reporting of Observational Studies in Epidemiology (STROBE) (25), and the guidance from Pulmonary, Critical Care and Sleep journals on causal inference and prediction research (26,27).

### Statistical analysis plan

A sample size of 300 patients was initially anticipated. As the epidemic in Sao Paulo grew fast, the hospital included new ICU beds, and we revised the anticipated sample size to 500 patients. Given that the study carries no risks for participants and that the requirement for informed consent was waived by the IRB, we intend to collect data on all patients with COVID-19 admitted to the ICUs during the study period, a sample possibly larger than the anticipated sample size. Such a large sample would suffice to allow identification of predictors of survival.

Categorical variables will be expressed as counts and percentages, and continuous variables, as mean (standard deviation) or median (interquartile range), as appropriate. All hypothesis tests will be two-tailed, with a significance level of 0.05, and they will be performed using the R software (R Core Team, 2016, Vienna, Austria). We will build Kaplan-Meier curves to estimate 28-days survival. ICU survival will be defined as the time interval between ICU admission and patient death from any cause or ICU discharge. Time will be censored at 28 days for patients who are still alive. Hospital survival will be defined as the time interval between ICU admission and patient death from any cause or hospital discharge. Patients discharged home will be considered alive at day 28. We will perform survival analysis using the Cox proportional hazards model censored at 28 days to identify the main risk factors for ICU survival beyond expected associations, such as age, comorbidity burden, and severity of disease at ICU admission. Variables identified *a priori* as clinically relevant (Table 5) and additional variables with a *p*-value <0.20 in a univariate analysis will be evaluated as independent risk factors of poor prognosis in a multivariable Cox model. The order of inclusion of variables into Cox multivariable models will follow statistical significance criteria and clinical relevance. Alternative models will be chosen on the basis of information criteria and likelihood ratio-based tests. Wherever possible, continuous variables will be modeled to account for nonlinearity with splines or polynomials and avoiding dichotomization. Additivity will be addressed with interaction terms. The proportional hazards assumption will be tested using Schoenfeld residuals. We will use mixed models to analyze the impact of ventilatory variables collected during hospitalization on the main clinical outcomes. We will perform complete case analyses, without missing data. We will also perform a sensitivity analysis using multiple imputation.

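### Survival times end at live discharge, whose status is undefined and at odds with the day-28 rules; if it is censored, Kaplan-Meier overstates mortality

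*Protocol article*

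**What the plan says.** The Outcomes section names the main outcome: "The main outcome is ICU survival at 28 days". The last items on its list of secondary outcomes are "ICU complications, and hospital survival at 60 days".

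The Statistical analysis plan section defines the two times:
- ICU: "ICU survival will be defined as the time interval between ICU admission and patient death from any cause or ICU discharge".
- Hospital: "Hospital survival will be defined as the time interval between ICU admission and patient death from any cause or hospital discharge".

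It adds two rules tied to day 28:
- "Time will be censored at 28 days for patients who are still alive".
- "Patients discharged home will be considered alive at day 28".

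The Abstract (Methods) says: "We will plot Kaplan-Meier curves to estimate ICU and hospital survival". The Statistical analysis plan section also plans a Cox model for ICU survival, censored at 28 days. Table 5 presents the variables as predictors of 28-day ICU survival and takes its p-values from univariate Cox models. On follow-up, the Data collection section says: "We will follow up patients to register vital status at 60 days or at hospital discharge, whichever occurs first". No competing-risk method is named.

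**The concern.** Under the two definitions, the clock stops at live discharge as well as at death. A patient who leaves the ICU alive can no longer die in the ICU, so live discharge is a competing event for ICU death. The plan gives it no status. Two codings fit the definition, and neither yields 28-day ICU survival:

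- Discharge as an event: the curve is a length-of-stay curve.
- Discharge as censoring: Kaplan-Meier assumes that discharged patients would have gone on dying at the rate of those still in the unit. They left because they were better, so the censoring is informative and mortality is overstated.

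The two day-28 rules point to a third coding, in which live discharges stay event-free to day 28, but they do not settle it. Two analysts could follow the same text and report very different values for the main outcome. The study intends to compare its survival with an external benchmark of 35%-45% hospital mortality in ventilated patients (Discussion). That range is only 10 points wide, so the coding alone could decide the comparison.

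**Working it through.** The plan gives no survival or discharge figure to reproduce, so the check has a textual part and a part based on assumed inputs.

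**1. Which patients do the day-28 rules cover?**

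| Patient | Covered by a rule? |
|---|---|
| Still in the ICU on day 28 | Yes, censored at day 28 |
| Discharged home before day 28 | Yes, counted alive at day 28 |
| Discharged from ICU to a ward, or transferred | Not clearly |
| Discharged alive from hospital, 60-day outcome | No; the only discharge rule stops at day 28, 32 days short (60 - 28) |

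The censoring sentence could be read to carry everyone discharged alive to day 28. On that reading, ending ICU time at ICU discharge would have no effect and the separate rule for patients sent home would be redundant. The sentences therefore do not fit together.

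**2. Size if discharge is censored at its own time.** Let F be the true cumulative incidence of death in the unit and S the share still in the unit at the horizon. With proportional cause-specific hazards, deaths make up F/(1 - S) of all exits, and

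1 - KM = 1 - S^(F/(1 - S)).

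F = 35-45% is borrowed from the benchmark in the Discussion. S is assumed throughout, because the documents give no discharge rate or timing.

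- F = 35%, S = 20%: 1 - 0.20^(0.35/0.80) = 50.5%.
- F = 40%, S = 12%: 1 - 0.12^(0.40/0.88) = 61.9%.
- F = 45%, S = 5%: 1 - 0.05^(0.45/0.95) = 75.8%.

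| Still in unit | F = 35% | F = 40% | F = 45% | Overstatement (points) |
|---|---|---|---|---|
| 30% | 45.2% | 49.7% | 53.9% | 8.9 to 10.2 |
| 20% | 50.5% | 55.3% | 59.6% | 14.6 to 15.5 |
| 10% | 59.2% | 64.1% | 68.4% | 23.4 to 24.2 |
| 5% | 66.8% | 71.7% | 75.8% | 30.8 to 31.8 |

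With 5-20% remaining, the overstatement is about 15 to 32 points.

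**3. Without proportional hazards.** A simulation of 400,000 patients used gamma-type event times within 28 days, with F = 35-45% and S = 5-20%. Nominal mean times before truncation at day 28 were 8 and 14 days.
- Deaths earlier than discharges (8 against 14): +9.5 to +19.1 points.
- Discharges earlier than deaths (14 against 8): +18.9 to +43.0 points.

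Over all cases with F = 35-45% and S = 5-30%, the range is about 9 to 43 points.

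**4. The other two codings.**
- Discharge as an event: with 10% still in the unit, 90% have had an event, whatever the mortality.
- All live discharges event-free to day 28: the estimate equals the observed share who died in the ICU, and the bias is 0.

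**5. The Cox model.** Take two groups with an assumed daily death hazard d = 0.03 and discharge hazards r = 0.03 and 0.12. ICU mortality at day 28 is d/(d + r) × (1 - exp(-28(d + r))):
- r = 0.03: 0.5 × (1 - exp(-1.68)) = 41%.
- r = 0.12: 0.2 × (1 - exp(-4.2)) = 20%.

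The cause-specific hazard ratio for death is 1.0, yet 28-day ICU mortality differs about twofold.

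**The case against.** The strongest reply is that the censoring sentence directly follows the ICU definition and speaks of patients still alive, without limiting this to those still in the ICU. Read that way, together with the discharged-home rule, every live discharge runs event-free to day 28 and there is no bias in the main outcome. This is a possible reading, and it rules out saying flatly that the planned analyses fail to estimate 28-day ICU survival. It does not settle the matter, because it empties part of the definition of meaning and still leaves day 60 without a rule.

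Four further points stand in whole or in part:

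- A reader might infer a fixed overstatement of 15 to 30 points. The documents do not support one, since they give no discharge rate, remaining share or timing.
- A reader might infer that the Cox results are invalid. They are not. With discharge censored, the model gives a proper cause-specific hazard ratio, a recognised target in a search for risk factors. What fails is reading that ratio alone as an effect on 28-day ICU survival, as the title of Table 5 invites. No 60-day hospital Cox model is stated, so the hospital problem concerns Kaplan-Meier only.
- Table 4 also reports ICU and hospital mortality as counts and percentages, and these do not depend on the censoring. They could, however, visibly disagree with the curves.
- A condensed article may leave event coding to a fuller plan. Here, though, the article itself states a definition under its own analysis-plan heading, and that definition conflicts with the sentences after it.

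**Conclusion.** The point holds in conditional form. The definitions of ICU and hospital survival time end at live discharge, give it no status and conflict with the plan's own day-28 rules. No rule carries live discharges to day 60.

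The consequence depends on the coding chosen. At day 28 it is nil if all live discharges are carried forward. The curve is a length-of-stay curve if discharge is an event. If discharge is censored, mortality is overstated by the amounts worked out above, which rest on assumed inputs and not on trial data. Because this concerns the main outcome and two of the three codings give a wrong result, it should be corrected before analysis.

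**What to change.** Reconcile the sentences in the Statistical analysis plan section as follows.

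- **ICU outcome.** Define the event as death in the ICU by day 28. Treat every live ICU discharge, whether home, to a ward or by transfer, as free of ICU death to day 28. Equivalently, estimate the cumulative incidence of ICU death (Aalen-Johansen) with live discharge as a competing event. Describe such patients as free of ICU death and not as alive, because a death on the ward before day 28 is possible and belongs to the hospital outcome.
- **Hospital outcome.** Apply the same rule to day 60 and label the result in-hospital mortality to day 60, since vital status is not followed after hospital discharge.
- **Cox model.** State how live discharge is coded in the 28-day model and interpret the hazard ratio to match. If discharge is censored, report cause-specific hazard ratios for death and for live discharge side by side, and retitle Table 5 accordingly.

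The cost is wording and the recoding of the time and status variables. ICU discharge status and vital status to hospital discharge or day 60 are already to be collected, so no new data are needed.
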